#### Design of the study

The study was designed as a double blind, parallel-group, randomized controlled trial (allocation ratio 1:1) starting before 28 weeks of pregnancy with a follow up of two and a half years. All data were handled confidentially. The Committee of Ethics on Human Research of the VU University medical center (Amsterdam, the Netherlands) approved the study design, protocols, information letters and informed consent form.

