#### Sample size

Sample size calculation was based on finding effect in smoking cessation at the time of birth, 12 months and 24 months post partum. The numbers in the formula were based on findings from the effect study of the NFP[50]. In order to detect an average improvement of decreasing smoking by 4 cigarettes a day with a standard deviation of 8 cigarettes, a power of 80% and an alpha of 5% were used. This resulted in a sample size of 57. Given the fact that 25% of all women smoke at the start of the pregnancy, 228 participants in the control group and 228 participants in the intervention group should at least complete the pregnancy-component.

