## Discussion

This article presents the design of the Nurse Family Partnership (NFP) intervention in the Netherlands. The program material of the NFP has been translated and culturally adapted to fit in the Dutch health care system and is called VoorZorg. In addition, a two-stage selection procedure has been designed to include mothers-at-risk for abusing their child. The feasibility of the VoorZorg intervention was evaluated positively in a pilot study. At the moment an RCT is conducted to study the effectiveness of the VoorZorg program. It is hypothesized that with the VoorZorg program risk factors operating during pregnancy and early childhood that compromise fetal and early child development are addressed.

Strengths of this study include the random controlled design and the communication between different stakeholders and several experts (research and practice). An additional strength is that the program was first tested for feasibility in a pilot study. In this way the program could be improved in the last phase. Furthermore, the study results are generalisable for all high risk pregnant women, because this study is conducted in the practice setting and in different regions in the Netherlands and carried out in both urban and rural areas.

This study has some limitations as well. One is that each phase is financed by a different organization. This is not efficient because each project must be accounted for separately. Another limitation was that the effect study on VoorZorg was conducted by a University Medical Center in Rotterdam and during the study a different University Medical Center took over the project. However, the project manager of VoorZorg stayed involved in the study and continued to be a co-author. Also, some of the interviewers did not stay throughout the RCT. Participants were sometimes difficult to motivate to participate in the study, especially in the control group. Therefore, interviewers experienced several difficulties in making appointments for the measurements. It is for that reason that it is important to teach interviewers strong motivation skills.

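### The 80% power is tied to smoking at birth, 12 and 24 months, but the 228 per arm it rests on are required only to the end of pregnancy, with almost no reserve for later loss

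*Protocol article*

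**What the plan says.** All of the planning inputs stand in one paragraph, the Sample size section of the protocol article.

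- Time points: "Sample size calculation was based on finding effect in smoking cessation at the time of birth, 12 months and 24 months post partum".
- Effect: "an average improvement of decreasing smoking by 4 cigarettes a day with a standard deviation of 8 cigarettes".
- Error rates: "a power of 80% and an alpha of 5% were used", with no statement of one or two sides.
- Result: "This resulted in a sample size of 57".
- Scaling: "Given the fact that 25% of all women smoke at the start of the pregnancy", which turns 57 smokers into 228 women.
- Requirement: "228 participants in the control group and 228 participants in the intervention group should at least complete the pregnancy-component".

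The Design of the study section describes a trial "with a follow up of two and a half years". The Randomization section reports 460 women, 237 to intervention and 223 to control. The Study population section allows withdrawal at any time. The Discussion adds: "Participants were sometimes difficult to motivate to participate in the study, especially in the control group".

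The Smoking cessation section, under the primary outcomes, asks about smoking at 16 to 28 weeks, at 32 weeks and at 2 months after birth. At two years, smoking appears only as one component of the secondary outcome, the number of risk factors.

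**The concern.** A calculation said to serve an effect at 24 months needs its women at 24 months. Here the head-count is fixed about two years before the last time point it is meant to cover, and enrolment barely exceeds it. A smoking comparison at 12 or 24 months that showed no difference could then be read against 80% power that the design does not secure at those times.

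This is separate from how 57 was obtained. Even if 57 smokers per arm did give 80%, the requirement as worded would not carry that power past the end of pregnancy.

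**Working it through.** **1. The plan's figures.** 57 / 0.25 = 228 per arm, which agrees with the article; 2 x 228 = 456. The 57 itself does not follow from the stated inputs by the usual formula: n per arm = 2 x (8/4)^2 x (1.96 + 0.8416)^2 = 62.8, so 63 two-sided (50 one-sided). That is a different problem, so step 3 takes 57 = 80% as given.

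**2. Reserve at randomization.**
- In total: 460 - 456 = 4 women (0.9%).
- By arm: intervention 237 - 228 = +9; control 223 - 228 = -5.
- Expected smokers at 25%: 237 x 0.25 = 59.25 and 223 x 0.25 = 55.75. The equal-arm equivalent is 2 / (1/59.25 + 1/55.75) = 57.4 per arm.

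The imbalance therefore costs almost no power in itself. The reserve over 57 is 0.4 / 57.4, or about 0.8%.

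**3. Power after loss, taking 57 = 80% at face value.** The article gives no loss rate, so 10% to 30% is an assumption. For a two-sided comparison at one time with a fraction L lost from each arm, power = Phi(2.8016 x sqrt(1 - L) - 1.96).

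| Assumed loss after pregnancy | Smokers per arm | Power |
|---|---|---|
| 0% | 57 | 80% |
| 10% | 51.3 | Phi(0.698) = 76% |
| 20% | 45.6 | Phi(0.546) = 71% |
| 30% | 39.9 | Phi(0.384) = 65% |

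**4. Power computed directly from a difference of 4 and SD 8** (two-sided t-test). With 57 per arm it is 75% with no loss, then 71%, 66% and 60% at 10%, 20% and 30% loss. With the actual arms it is 76%, 71%, 66% and 60%. About 5 points of this shortfall are present with no loss and belong to the 57-versus-63 problem, so this series must not be read as the effect of loss alone.

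**5. What would offset the loss.**
- *Smoking proportion.* To keep 57 smokers per arm from 228 women after loss L, the proportion must be 0.25 / (1 - L): 28%, 31% and 36% at 10%, 20% and 30% loss. With 40% smokers, the actual arms and 30% loss, direct power is about 80%.
- *Repeated measurements.* With three measurements, n = 62.8 x (1 + 2 rho) / 3 equals 57 when rho is about 0.86. Suppose 30% of women then lose both later measurements at random and the effect is the same at all times. Information per woman is 0.7 x 3/2.72 + 0.3 x 1 = 1.072, and power is Phi(0.5 x sqrt(57 x 1.072 / 2) - 1.96) = 79%.

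**The case against.** The strongest reply is that the article never says 80% at each time separately. The paragraph can be read as one calculation over three measurements, and the Analyses section plans multilevel models for longitudinal data. On that reading a woman lost after birth still contributes her first measurement, and 30% loss costs about one point of power. This stands as a possibility. However, the Sample size section states neither a repeated-measures basis nor a correlation, and the reading needs a correlation of about 0.86 to reach 57. It also gives power for an effect common to all three times, not for an effect at 24 months.

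Second, the 25% refers to all women, whereas smoking in pregnancy is one of the qualifying risk factors and the Background says that women of low socio-economic status use substances more often. More smokers than planned is plausible and could remove the shortfall. This also stands, but the stated power has to be judged on the stated proportion.

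Third, the article schedules no primary smoking measurement after 2 months postnatal, and for those times a pregnancy-completion count is close to the right horizon. That is correct. It turns part of the point into a contradiction over time points, which the fix must cover.

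Fourth, a condensed article may leave its allowance for loss to the full protocol. No fault is found with a missing allowance. The fault is that one paragraph names 24 months and sets its count at the end of pregnancy.

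Two stronger readings are tempting and not supported. A reader might infer that every 24-month primary outcome is underpowered. The calculation claims power for smoking only, and child-abuse reports come from a reporting agency, so missed interviews need not remove them. A reader might also take the Discussion's remark about motivation as evidence of a particular loss. It describes difficulty in recruiting effort and appointments and gives no rate.

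**Conclusion.** The point holds in a limited form. On the plan's own 25% and a comparison at a single time, the design secures its required count only to the end of pregnancy. The control arm starts 5 below that count, and the overall margin is under 1%. Any material loss after birth then takes power at 12 and 24 months below 80%: about 76% to 65% for an assumed 10% to 30% loss, with 57 = 80% taken at face value.

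The direction follows from the article; the size rests on the assumed loss. It also rests on a two-sided test. Computed directly one-sided, 57 per arm would have about 85% power and would fall below 80% only at about 15% loss. A higher smoking proportion or a longitudinal analysis could offset part or all of the fall. The documents do not show that power at 24 months was in fact any particular figure.

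**What to change.** In the Sample size section:

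1. State that the 228 per arm and the 80% attached to it apply to the end of pregnancy only.
2. Give the power at 12 and 24 months for the actual arms (237 and 223) and the retention achieved or, until that is known, for a range such as 10% to 30% loss. State the sidedness and the smoking proportion used. If a longitudinal analysis is the basis, state the correlation and whether the power is for an average effect or for the effect at a given time.
3. Reconcile the birth, 12-month and 24-month time points with the Smoking cessation section, which measures smoking as a primary outcome only to 2 months postnatal. If no primary smoking comparison is intended at the later times, remove them from the power statement.

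The cost is wording and, if the later times are kept, probably a less favourable stated power. No further enrolment is called for.

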#### Randomization

A total of 460 women were included and randomized in strata by region and ethnicity into a control or intervention group by a researcher of the VU University medical center. Randomization was made blind by using a computer-generated list of random numbers (0, 1) in software SPSS 14.0 [51]. The researcher then informed the VoorZorg nurse about allocation. 237 women were assigned to the intervention group and were visited by trained VoorZorg nurses. 223 women were allocated to the control group and received the care as usual. A flow-chart of the RCT is shown in Figure 2. Women who lived in the same house as another participant of VoorZorg were not randomized but assigned into the same treatment group to prevent contamination. This was relevant for one respondent who was assigned to the intervention group without randomization.

**Figure 2 F2:**
[figure not shown]
**Flow of the participants through the study**.* General Practioners, gynaecologists, midwifes, street corner workers etc.

#### Analyses

The effectiveness of the VoorZorgprogram compared to care as usual will be analyzed with different statistical methods, using intention to treat analyses. Logistic Regression analyses will be used for comparing proportions between the intervention group and control group (smoking cessation, birth outcome, domestic violence and child abuse). Linear Regression analyses will be used for comparing means between the intervention and control group (numbers of cigarette smoked, birth weight, gestational age, child development and number of risk factors for child abuse). Multilevel analyses will be used for analyzing longitudinal data. The multilevel and regression analyses using the (longitudinal) data as dependent variables were adjusted for possible confounders and were also checked for possible effect modification like age and ethnicity.

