#### Home visits

VoorZorg consists of approximately 10 home visits during pregnancy, 20 during the first life year of the child and 20 during the second life year. The visits are conducted by trained VoorZorg nurses. The visits are more frequent during the first month of the intervention and six weeks after birth, because these periods are important for the mother. The duration of each visit is between one hour and one and a half hour. The purpose of the visits is: structured behavioral changes, health education, discussing questions of the expectant mother, setting and maintaining realistic and achievable goals, increasing the mother's self-efficacy and involving the social network of the mother into the program. The VoorZorg nurses use three manuals that were designed for pregnancy, infancy and toddlerhood and focus on six domains: health status of the mother, child's health and safety, personal development of the mother, the mother as a role model, relation of the mother with her partner, family and friends and use of institutions. Each manual contains a full description of the visit. However, the visits are flexible and nurses are able to improvise when needed. It is important that VoorZorg nurses maintain a good relationship with the mother throughout the program.

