#### Training of the VoorZorg nurses

At the end of this phase twenty-five certified nurses were recruited by Youth Health Care organizations in twenty municipalities. The nurses were requested to comply with specified competences, including having a minimum of two years of working experience, affinity with high risk families, and experience with teaching parenting skills. All nurses received the following trainings to become a VoorZorg nurse: Video Home Training, training for pregnancy-, infant- and toddler period, and training about reducing smoking behavior with minimum intervention strategies (V-MIS). The trainers applied the training material that was used in the NFP.

In addition to these trainings, supervision at work on a weekly basis was a requirement for the execution of the program. The VoorZorg nurses were able to discuss difficulties in the implementation of the program with trained supervisors from their institution once a week. They could also discuss cases with other VoorZorg nurses during case conferences at the national level organized five times a year. The trainer or supervisor of the NJi could also be consulted. The maximum caseload for VoorZorg nurses with a full-time employment was 18 mothers.

### PHASE 3

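### The regressions stated for single-time outcomes treat women as independent, although each nurse serves about 9.5 intervention women; standard errors are understated if outcomes vary by nurse beyond regional differences

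*Protocol article*

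**What the plan says.** The Analyses section of the protocol article assigns outcomes to models. Logistic regression is named for smoking cessation, birth outcome, domestic violence and child abuse. Linear regression is named for number of cigarettes, birth weight, gestational age, child development and number of risk factors. Of multilevel modelling it says: "Multilevel analyses will be used for analyzing longitudinal data". No nurse, organisation or region term is named. Adjustment is for possible confounders, not listed beyond age and ethnicity, which appear as examples of effect modifiers.

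The delivery structure is given elsewhere:

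- Training of the VoorZorg nurses: "twenty-five certified nurses were recruited by Youth Health Care organizations in twenty municipalities", and "The maximum caseload for VoorZorg nurses with a full-time employment was 18 mothers".
- Randomization: "237 women were assigned to the intervention group and were visited by trained VoorZorg nurses", whereas "223 women were allocated to the control group and received the care as usual".
- Randomization again: women were "randomized in strata by region and ethnicity into a control or intervention group", so the unit is the individual woman.
- Home visits: about 10 visits in pregnancy and 20 in each of the child's first two years. The manuals describe each visit, but "the visits are flexible and nurses are able to improvise when needed".

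The Sample size section contains no allowance for clustering.

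**The concern.** In this programme the nurse is the vehicle of treatment. Women who share a nurse share her skill, her style and her judgement about when to depart from the manual, so their outcomes may be correlated. Control women have no VoorZorg nurse. The data are thus nested in one arm only, which is a partially nested design.

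Ordinary logistic or linear regression ignores that correlation. If it is positive, the intervention arm carries less information than 237 independent women would, confidence intervals are too narrow, and the test rejects too often when the average effect is zero. The point bears most on outcomes recorded once in all women. These include agency-reported child abuse, whose prevention is the programme's main goal.

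**Working it through.** **The plan's own figure.** The article gives no ICC and no design effect. Its only relevant number is the sample size: 57 smokers, scaled as 57/0.25 = 228 women per arm. That scaling reproduces and contains no clustering term. (The 57 itself does not follow from a difference of 4, SD 8, 80% power and two-sided 5%: 2 × [8 × (1.960 + 0.842)/4]² = 62.8, so 63 per arm. That is a separate matter.)

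**Inputs from the article.** 25 nurses, 237 intervention women, 223 controls, 25% smokers.

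**Assumptions.** Nurse ICC of 0.01, 0.05 or 0.10; equal caseloads; the 25 recruited nurses are those who delivered the trial intervention.

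**Step 1. All women, ICC entirely nurse-specific.**

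- Women per nurse: m = 237/25 = 9.48
- Design effect, intervention arm only: DE = 1 + (m − 1) × ICC
- True over naive standard error: R = √[(DE/237 + 1/223) / (1/237 + 1/223)]
- Understatement: 1 − 1/R
- True type I error of a nominal 5% test: 2 × [1 − Φ(1.96/R)]

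For ICC = 0.05: DE = 1 + 8.48 × 0.05 = 1.424, and R = √(0.010493/0.008704) = 1.098.

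| Assumed ICC | DE | R | SE understated by | Type I error |
|---|---|---|---|---|
| 0.01 | 1.08 | 1.02 | 2% | 5.5% |
| 0.05 | 1.42 | 1.10 | 9% | 7.4% |
| 0.10 | 1.85 | 1.19 | 16% | 9.9% |

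**Step 2. Smokers only.** With 25% smokers, m = 0.25 × 237/25 = 2.37. At ICC 0.10, DE = 1 + 1.37 × 0.10 = 1.137. With both arms reduced to a quarter, R = 1.033 and type I error is 5.8%. At ICC 0.01 it is 5.1%.

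**Step 3. Part of the ICC is regional.** Randomisation was stratified by region, so variation shared by both arms of a region largely cancels from the comparison. Suppose an ICC of 0.05 is 0.03 region plus 0.02 nurse-specific, with total variance 1 and arms balanced within region.

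- Intervention variance per woman after cancellation: 0.95 + 0.02 × 9.48 = 1.140
- Control variance per woman after cancellation: 0.97
- R = √[(1.140/237 + 0.97/223) / (1/237 + 1/223)] = 1.026, giving type I error of 5.6% (5.5% if the control variance is taken as 0.95)

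If the whole 0.05 were regional, R = √0.95 = 0.975 and type I error would be 4.4%, so the naive test would be slightly conservative.

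**The case against.** **No ICC is given.** The size of the effect rests on an assumed value, and the lower end of the range (5.5%) is negligible. If the programme changes nothing with any nurse, the nurse adds no variance and there is no inflation from this source. This stands: the finding is conditional.

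**Region absorbs part of it.** There are 25 nurses in twenty municipalities and women came from 20 regions, so nurse and area probably overlap heavily. Step 3 shows that the overlap can bring 7.4% down to about 5.5%, or below 5%. This also stands, and it is why the nurse-specific part is what counts.

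**Delivery is standardised.** Manuals, common training, weekly supervision and national case conferences should all limit variation between nurses, and the pilot found that nurses could follow the guidelines. Birth outcomes follow only about 10 visits, not the full 50 or so. These points argue for a small ICC, but do not show that it is zero.

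**Silence in a condensed article.** A reader might infer that the longitudinal multilevel models also omit the nurse. The article does not name their levels, so that is not supported. The single-time regressions differ: there the article states the model, and ordinary regression assumes independence.

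**Other stronger readings.** A reader might conclude that standard errors are too small as a fact, that type I error exceeds 5% for every outcome, or that results could not extend beyond these 25 nurses. The first two need a positive nurse-specific ICC, which is not documented. The third turns a choice between fixed and random nurse inference into a defect.

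**Conclusion.** The point holds in conditional form and for a limited set of outcomes. For single-time outcomes in all women, the stated regressions do not match the delivery structure described in the same article. If outcomes vary between nurses beyond regional differences, standard errors are understated by about 2% to 16%, and type I error is 5.5% to 9.9%, for a nurse-specific ICC of 0.01 to 0.10. These figures assume equal caseloads of about 9.5; unequal caseloads would raise them, and a regional share of the ICC would lower them. For the smokers' endpoint the type I error is at most about 5.8%. For longitudinal outcomes the claim is not established. It is a worthwhile correction to the analysis, and does not by itself invalidate the trial.

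**What to change.** For birth outcomes, agency-reported child abuse, child development and any other outcome measured once in all women:

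- Fit a partially nested mixed model (linear or logistic), with a random nurse effect in the intervention arm only, controls as singletons, and small-sample degrees of freedom.
- Include the stratification factors, region and ethnicity, as covariates, so that regional variation is not counted as nurse variation.
- Report the estimated nurse ICC for each outcome.
- For uncommon binary outcomes where this model is unstable, use cluster-robust standard errors with a small-sample correction, or present the nurse model as a sensitivity analysis.
- State the levels of the longitudinal multilevel models.

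The cost is a revised model statement and a nurse identifier for each intervention woman; the article does not say whether one is recorded. Intervals will be slightly wider if the ICC is positive, and convergence problems are possible for rare outcomes, with only about 9 women per nurse. If the ICC is near zero, results will hardly change and robustness will have been shown.
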